#### Economic evaluation

The evaluation will be undertaken from the NHS perspective. The health service use costs of the two strategies will be calculated at 18 months in both groups. Costs incurred between 12 and 18 months will be discounted at 3.5%, in line with NICE guidelines. The mean cost of the two groups over 18 months will be compared using non-parametric tests. Results will be reported with 95% confidence intervals and uncertainty will be examined using sensitivity analysis.

An incremental cost-effectiveness ratio will not be calculated over the 18 months of the intervention as this length of follow-up does not capture all relevant costs and outcomes. Consequently, without the use of modelling, a cost-effectiveness analysis could be misleading. The need or otherwise for cost-effectiveness modelling will depend on there being economically important clinically significant differences in glycaemic control, as determined by the likely impact on and hence, long-term effects on morbidity and mortality. Whether any differences in glycaemic control are important will be informed by reviewing the cost-effectiveness of other interventions that have been evaluated using lifetime models. If such differences do exist, the modelling of the longer-term effects to assess the incremental cost per quality adjusted life-year will be conducted.

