### Randomisation of practices

The study is cluster-randomised, with all enrolled participants in one practice randomised to one arm of the trial in order to avoid potential 'contamination' from participants randomised to different arms. Randomisation was carried out independently at the University of Leicester, after stratification for practice setting and list size. Two randomisation plans were computed, one for small and one for large lists sizes. ^a^Practices agreed to participate in the study before being randomised. Practices were not informed of their randomisation when recruited, but become aware of it during the study as participants attend the practice for clinical support and repeat prescriptions for monitoring resources.

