### Analysis

#### Power calculations and sample size

The aim is to show equivalence in mean HbA1c at 18 months of within ± 0.5%. Assuming a standard deviation (SD) at 18 months of 1.5%, [37] the sample size required without allowing for clustering for 80% power at 5% significance is 142 per arm. With an intra-cluster correlation of 0.05, [38] and an expected mean cluster size of 5, adjustment for clustering brings the number required to 170 per arm. Assuming 20% drop out and 20% non-consent, the numbers required are 266 referrals and 213 consents per arm.

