#### Statistical analysis

There will be double entry of all data and discrepant values will be investigated. Results will be reported according to CONSORT guidelines for cluster randomised trials and statistical analysis carried out on an intention-to-treat basis. Missing outcomes will not be replaced and an average over-time of continuous outcomes will be derived. This procedure will measure the cumulative effect of the treatment and have the maximum number of participants. Continuous variables will be analysed using a linear model adjusting for clustering using generalised estimating equations, and adjusting for baseline values.

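### The planned comparison of mean costs uses unnamed non-parametric tests: rank tests would not test the mean, and no allowance for randomisation by practice is carried over

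*Protocol article*

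**What the plan says.** The Economic evaluation section takes the NHS perspective and gives one sentence on how costs are compared: "The mean cost of the two groups over 18 months will be compared using non-parametric tests". The test is not named. The next sentence adds: "Results will be reported with 95% confidence intervals and uncertainty will be examined using sensitivity analysis". Neither sentence mentions practices.

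Elsewhere the article takes clustering into account. Randomisation of practices states: "The study is cluster-randomised, with all enrolled participants in one practice randomised to one arm of the trial". The sample size is inflated "With an intra-cluster correlation of 0.05, [38] and an expected mean cluster size of 5". The Statistical analysis section says: "Continuous variables will be analysed using a linear model adjusting for clustering using generalised estimating equations, and adjusting for baseline values", and commits to reporting under the CONSORT extension for cluster trials.

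**The concern.** There are two separate problems in one sentence.

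**The quantity.** From a payer's perspective the quantity of interest is the arithmetic mean, because total spend is mean cost times number of patients. The sentence names the mean, but in a two-group comparison its method is ordinarily read as a rank test. A rank test asks whether a cost drawn from one arm tends to exceed a cost drawn from the other. It answers a question about means only if the two distributions have the same shape. That cannot be assumed here. Participants choose how often to test and may swap methods or stop (Development and piloting of self-monitoring sessions), and the article describes urine testing as the cheaper method. The p-value and the reported mean difference could then disagree.

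**The unit.** Practices were randomised and practices issue the repeat strip prescriptions, so costs may be correlated within practice. The GEE sentence describes a linear model, whereas the economic section names a different class of method. The adjustment therefore does not carry over automatically.

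The cost comparison is secondary but not trivial. The Background asks whether a cheaper method could do as well. No 18-month cost-effectiveness ratio is planned, and modelling follows only if glycaemic control differs importantly. If HbA1c proves equivalent, the comparison of mean costs is the main economic result.

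**Working it through.** **Inputs from the protocol article.** Power calculations and sample size: margin 0.5%, SD 1.5%, 80% power, 5% significance, intra-cluster correlation (ICC) 0.05, mean cluster size 5, 20% drop-out, 20% non-consent. There is no cost mean, cost SD or cost ICC.

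**The plan's own figures reproduce.**
- Unclustered: 2 × [1.5 × (1.960 + 0.842) / 0.5]² = 141.3, so 142 per arm.
- Design effect: 1 + (5 − 1) × 0.05 = 1.20, and 142 × 1.20 = 170.4, stated as 170.
- 170 / 0.8 = 212.5, stated as 213 consents; 213 / 0.8 = 266.25, stated as 266 referrals.

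The design effect of 1.20 is therefore the protocol's own working value, although it was set for HbA1c.

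**Check 1: does a rank test answer a question about means?** Assumptions: log-normal costs, 170 independent participants per arm, the same true mean in both arms, and log-SDs that may differ. The level of the mean does not affect the result; the log-SDs drive it. A log-normal cost with mean M and log-SD s has median M × exp(−s²/2). Equal means with unequal s therefore give unequal medians, and the rank test responds to that. With M = 400 (illustrative) and log-SDs 0.6 and 1.0, the medians are 400 × exp(−0.18) = 334 and 400 × exp(−0.5) = 243.

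Simulated proportion of trials with p < 0.05 (at least 2,000 trials per setting, rounded):

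| Log-SD in the two arms | Mann-Whitney | Welch test of means |
|---|---|---|
| 0.8 and 0.8 | about 5% | about 5% |
| 0.6 and 0.7 | about 15% | about 5% |
| 0.8 and 0.9 | about 15% | about 5% |
| 0.7 and 0.9 | about 44% | about 5% |
| 0.6 and 1.0 | 93% | about 7% |

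These trials have equal means, so they show rejection without a difference in means. They do not show a reversal of direction. Reversal needs a further assumption, that the arm with the higher median has the lower mean. One such case has medians 100 and 80 and log-SDs 0.5 and 1.0, so the means are 100 × exp(0.125) = 113 and 80 × exp(0.5) = 132. Mann-Whitney then significantly called the arm with the lower true mean the dearer one in 70% of 2,000 trials. With medians 100 and 90 and the same log-SDs, it did so in 23%.

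**Check 2: what does ignoring practice cost?** If the variance is understated by a design effect DE, a nominal two-sided 5% test has true level 2 × [1 − Φ(1.96 / √DE)]. With cluster size 5:

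| Assumed cost ICC | DE | 1.96 / √DE | True level |
|---|---|---|---|
| 0.01 | 1.04 | 1.922 | 5.5% |
| 0.05 | 1.20 | 1.789 | 7.4% |
| 0.10 | 1.40 | 1.657 | 9.8% |

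A simulation of Mann-Whitney on clustered log-normal costs (34 practices of 5 per arm, identical arms, 4,000 trials) gave 4.8% at ICC 0, 7.1% at 0.05 and 9.5% at 0.10, in line with the formula. At DE 1.20 an unadjusted interval has 1 / √1.20 = 0.91 of the proper width, so it is about 9% too narrow.

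A participant-level bootstrap of the mean does target the mean but does not deal with practice. It rejected in 7.5% of trials at ICC 0.05 and 6.1% at ICC 0. With 1,000 trials each, that difference is within simulation error, so the formula is the better guide.

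**The case against.** Non-parametric does not have to mean rank-based. The sentence says means are compared, and the next one promises confidence intervals. A non-parametric bootstrap fits both statements, and a permutation test of the mean difference fits the first. Under either, the first half of the concern falls. This stands: the text does not name a rank test, so it cannot be said that the plan tests the wrong quantity, only that on the ordinary reading it would.

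On clustering, the article is silent; it does not say that costs will be treated as independent. The commitment to cluster reporting could be taken to cover costs, and an article may leave such detail to a fuller plan. That stands in part. However, the economic section names a method, and that method is not the GEE linear model, so a reader following the text has no adjustment to apply.

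Three stronger readings are tempting and are not supported. A reader might infer that the cost result will be wrong, or wrong in direction; this depends on cost shapes for which the article has no data. A reader might take 93% as the expected error rate; it is the extreme of an assumed range that starts at about 5%. And a reader might infer that cost decides the recommendation if HbA1c is equivalent; Implications of the hypothesis ties the recommendation to the HbA1c result, and no decision rule rests on the cost p-value.

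**Conclusion.** The concern holds in a conditional form.

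- **If rank tests are meant**, the method does not match the stated quantity. Under assumed log-normal costs with equal means, false indications of a difference in mean cost run from about 5% (same shape), through 15% to 45% (small to moderate differences in shape), to 93% (a large difference).
- **If a test of means is meant**, that problem disappears.
- **In either case**, a participant-level analysis ignores the unit of randomisation. The true level is about 7.4% at the protocol's design effect of 1.20, and 5.5% to 9.8% for an assumed cost ICC of 0.01 to 0.10. This is a modest inflation, and the HbA1c ICC may not apply to costs.

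The sentence should be changed because it fixes a method that is ambiguous at best, in what may be the trial's main economic result.

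**What to change.** Replace the sentence with one stating that arithmetic mean 18-month costs per participant will be compared between arms, using either a bootstrap that resamples practices or a GEE or generalised linear model with practice-level robust standard errors. State that the 95% confidence interval for the difference in means comes from that same method, so that test and interval cannot disagree. If a rank comparison is kept, label it descriptive.

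The data are unchanged and participants and practices carry no extra burden. The price is slightly wider intervals (by a factor of about √1.20 = 1.10 if the HbA1c design effect applies to costs) and a little more analysis work.

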#### Qualitative sub-studies

In order to investigate the acceptability of the two monitoring methods, qualitative semi-structured interviews are being conducted with a small sample of participants including a similar number of those allocated to each monitoring method in the trial. The focus of this is to explore participants' views and experiences of using the allocated monitoring method (and the other method if they swapped) as part of their self-management of T2DM. Interviews are conducted approximately one year after attending the DESMOND SMBG programme.

In addition, focus groups and qualitative interviews are being conducted with a sample of the DESMOND educators involved in delivering the DESMOND SMBG intervention at different points throughout the trial period. The purpose of this is to explore educators' views and experiences of the trial including: the training and their delivery of the intervention, their views and preferences with regards to the two monitoring methods, and their reflections on delivering both arms of a trial while potentially not being in individual equipoise.

## Discussion

The DESMOND SMBG trial has been designed to provide additional evidence to inform the debate around the value of SMBG for people with Type 2 diabetes (T2DM) not using insulin or at risk of hypoglycaemia. Its particular strength is that it will allow us to assess the additional contribution of SMBG in people with newly diagnosed T2DM who are undertaking a quality assured structured education course delivered in primary care. Our hypothesis is that use of SMBG rather than urine monitoring in the context of delivering the DESMOND intervention will provide no added benefit in improving and sustaining glycaemic control over 18 months. Thus, we will be measuring any added benefit of SMBG (and its cost-effectiveness) over a clinically relevant period of follow-up while controlling for the other components of a complex intervention, in particular, the educational programme itself and feedback of glucose levels from another form of monitoring.

We will also compare the effect of the two self-monitoring methods on secondary outcome measures, including biomedical (systolic and diastolic blood pressure, lipid profile, body weight and waist circumference), and psychological (generic and disease specific well being, treatment satisfaction and perceptions about diabetes) measures. We will explore the views of participants concerning their experience of and preference for the two methods, and measure which self-monitoring strategy participants adopt over the subsequent 18 months. We will calculate the cost effectiveness of both methods.

Attitudes to self-monitoring are influenced by people's experience of the real world, as is the success or otherwise of their self-monitoring strategies. While our study is carefully planned and monitored, by virtue of the fact that it is embedded in the real world, it is in essence a pragmatic trial. The incorporation of questionnaires investigating psychosocial aspects and impact of self-monitoring will provide an important contribution to questions about acceptability of the methods; the findings of which will help illuminate the results of the main trial. The questionnaires will both record and monitor changes in self-monitoring strategies among the participants and the qualitative sub-study will seek a greater understanding of participant attitudes and preferences in respect of self-monitoring. Since the DESMOND education programme has been shown to be active in changing illness beliefs, [32] we will also be examining the benefit of SMBG within an education programme which has been set up to enable participants to exploit the benefits of feedback from direct measurement of their glucose levels. Finally to prevent potential contamination from attitudes of practice clinical staff we have undertaken cluster randomisation at the level of the practice.

Our trial is also exploring the effect of specific attention to the potential influence of educators' attitudes upon intervention delivery through targeted training and through assessment of attitudes and preferences. The training highlighted issues of potential bias in intervention delivery by specifically raising awareness of equipoise and by formally assessing educators' delivery of the intervention in both arms of the trial. A qualitative sub-study with the educators will enable us to investigate their attitudes towards and experiences of both the training they received and delivery of the intervention(s).

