The situation is much more uncertain for individuals with T2DM, particularly those managing their condition with lifestyle adjustments or using oral agents other than sulphonylureas. This uncertainty is reflected in the wide variation in the use of SMBG in different parts of the UK, [9] but even in areas where SMBG is used less often, the estimated costs are considerable, amounting to hundreds of thousands of pounds in an average primary care trust. It has been argued that providing such technology to those on tablets or diet is a waste of time and money since there is little an individual can do with the result [10]. Others believe strongly that the information provided by SMBG is a powerful motivating factor, [11] encouraging self-management by enabling people with T2DM to measure directly the effect of different actions, such as the effect of eating on post-prandial glucose or the glucose lowering effect of exercise. Previous studies have attempted to assess the contribution of SMBG to improved metabolic control in this group. Most, [12,13] but not all, [14] observational studies have shown that even in those managing their T2DM using diet alone, increased frequency of SMBG is associated with better outcomes including lowered glycated haemoglobin (HbA1c) and less mortality. This has been used to advocate SMBG for all those with T2DM [15]. However, these results may merely indicate that those who are highly motivated (reflected in the take-up of SMBG technology) are likely to do well in the long term.

Trials of interventions incorporating education about SMBG have reported mixed results. The DIGEM study reported no evidence of an effect of SMBG (with or without support from trained practice nurses in the interpretation and application of results) [16]. However, limitations included potential contamination due to lack of cluster-randomisation, a drop in adherence to SMBG over the study period, [17] and exclusion of people with prior experience of SMBG. Similarly, the ESMON study reported no evidence of an effect of structured education with or without additional education on self-monitoring [18]. Both studies reported a net adverse effect on anxiety/depression, suggesting that SMBG increased worry and depressed mood.

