### Implications of the hypothesis

The DESMOND SMBG trial will provide additional evidence to inform the debate around the value of SMBG for people with T2DM not using insulin or at risk of hypoglycaemia. In particular it will allow us to assess whether SMBG is equivalent to urine monitoring in people with newly diagnosed T2DM who are undertaking a quality assured structured education course delivered in primary care.

If the null hypothesis is not rejected, then SMBG will not be recommended for people with newly diagnosed T2DM. However, if the null hypothesis is rejected, and the results demonstrate that SMBG is equivalent to urine monitoring in terms improving and sustaining glycaemic control over 18 months, then this will be used as evidence to recommend SMBG for people with newly diagnosed T2DM who are undertaking the DESMOND intervention.

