## Methods/Design

The study is an 18 month multi-site cluster randomised controlled trial conducted in 8 sites in 7 PCTs in England, and managed by a central DESMOND Research Office. Ethical approval was received from Cambridgeshire Research Ethics Committee (07/H0304/129) and local research governance approval from participating PCTs.

Practices are randomised to one of two arms: 1) Participants attend a DESMOND structured education programme which includes a module on self-monitoring of blood glucose; and 2) Participants attend a DESMOND structured education programme which includes a module on self-monitoring of urine glucose.

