### Study intervention

The study intervention is the DESMOND Newly Diagnosed structured education programme with specific sessions on SMBG, compared with the same programme with specific sessions on self-monitoring of urine glucose [32]. The standard programme involves 6 h of contact time, facilitated by two trained HCPs. The content of the curriculum is designed for people attending within 12 weeks of diagnosis and focuses on cardiovascular risk factors and associated lifestyle factors, such as food choices and physical activity. The broad content of the curriculum has been reported elsewhere [33]. The HCPs attend a formal training programme in order to be accredited as DESMOND Educators [34]. A quality development pathway and specifically developed and tested quality assurance tools are used to ensure consistency of delivery.

The standard DESMOND Newly Diagnosed programme includes a 20 min session on self-monitoring which covers the difference between short term and long term monitoring of blood glucose, without detailed coverage of the different methods, and forms a relatively small part of the programme. However, for the purpose of the trial, the session on self monitoring has been extended in length and content. The development, piloting and content of the self-monitoring sessions for the trial and the training of the DESMOND educators are described below.

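### The two arms compare blood with urine monitoring, so the trial can estimate SMBG only relative to urine testing; the Discussion claims more, and an equivalence result alone cannot support recommending SMBG

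*Protocol article*

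**What the plan says.** Methods/Design sets out the allocation: "Practices are randomised to one of two arms". In the first, "Participants attend a DESMOND structured education programme which includes a module on self-monitoring of blood glucose"; in the second, "Participants attend a DESMOND structured education programme which includes a module on self-monitoring of urine glucose". No arm receives the programme without a monitoring module.

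The Discussion describes the trial's particular strength thus: "it will allow us to assess the additional contribution of SMBG in people with newly diagnosed T2DM" within a quality-assured education course. The next sentence gives a narrower contrast: "Our hypothesis is that use of SMBG rather than urine monitoring in the context of delivering the DESMOND intervention will provide no added benefit". The one after it says that the design controls for the education programme and for glucose feedback from the other kind of monitoring. Later, the Discussion again speaks of examining what SMBG offers inside an education programme, and does not name the comparator at that point.

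The section Implications of the hypothesis opens with a broad aim, "The DESMOND SMBG trial will provide additional evidence to inform the debate around the value of SMBG", and then narrows it to whether SMBG is equivalent to urine monitoring. It goes on to say that, if equivalence is shown, the result will serve as evidence for recommending SMBG to newly diagnosed people taking the programme. The margin, in Power calculations and sample size, is ±0.5% HbA1c at 18 months.

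**The concern.** What SMBG adds for people already receiving structured education is the difference between education with SMBG and education without monitoring. The trial has no randomised group of the second kind. The headline strength is therefore a property that the design lacks.

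This matters more in an equivalence trial than in one seeking a difference. If the arms differ, at least one method must be doing something. If they do not, the result is what two effective methods would give and also what two inert ones would give. Using equivalence as evidence for recommending SMBG assumes that urine testing is itself worth having in this setting, which the trial does not test. A report that follows the article's wording could present equivalence as proof that SMBG has value within education, with no data in the trial on that question.

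**Working it through.** No planned figure is attached to this claim, so the check is of what the two arms can identify.

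**Inputs**
- Two arms, both with the education programme and a monitoring module (Methods/Design).
- Margin ±0.5% HbA1c (Power calculations and sample size).
- Pooled HbA1c reductions over no SMBG of 0.21% for simple and 0.52% for enhanced SMBG, and no difference between blood and urine testing (Background).

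**Step 1: the contrast.** Let *e* be the mean HbA1c change with education alone, *b* the further change due to SMBG and *u* the further change due to urine testing.
- Blood arm: *e* + *b*
- Urine arm: *e* + *u*
- Difference: (*e* + *b*) − (*e* + *u*) = *b* − *u*

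The claim in the Discussion, read alone, concerns *b*. The trial estimates *b* − *u*.

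**Step 2: change from baseline does not help.** Within the blood arm it estimates *e* + *b*, and *e* is not observed separately in any arm.

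**Step 3: what equivalence means.** It means that *b* − *u* lies within ±0.5%. Assume for illustration that the Background's effects carry over and are the same for both methods:

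| *b* | *u* | *b* − *u* |
|---|---|---|
| 0 | 0 | 0 |
| −0.21% | −0.21% | −0.21 − (−0.21) = 0 |
| −0.52% | −0.52% | −0.52 − (−0.52) = 0 |

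The three cases look the same to the trial. Narrowing the margin does not separate them, because the difference is exactly zero in each.

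**Step 4: can outside evidence supply *u*?** The Background gives no figure for urine testing against no monitoring. One can chain the pooled SMBG effects to the finding that blood and urine testing do not differ, but three things weaken the chain.
- As the article describes it, enhanced SMBG includes education and feedback. It does not say whether the no-SMBG group received the same education, so 0.52% need not be an increment over education.
- For the study closest to this setting, the article says that "the ESMON study reported no evidence of an effect of structured education with or without additional education on self-monitoring".
- The article also reports that the DIGEM trial found no evidence of an SMBG effect.

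The outside evidence is therefore mixed on the quantity that the recommendation needs.

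**The case against.** The strongest reply is that the comparator is plain in context. The sentences after the headline claim set SMBG against urine monitoring, and the implications section narrows its opening aim in its second sentence. The objectives and hypothesis sections say the same. The Background's motivating question is whether a cheaper method could do as well, and two arms suit that question. This largely stands. The phrases about added benefit and informing the debate need little change. What it does not rescue is the headline sentence as written, the later unqualified phrase in the Discussion, or the step from equivalence to a recommendation.

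A second reply is that the Background gives some reason to think that monitoring is active. That also stands, as external evidence. It does not make an equivalence result evidence of activity.

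Several stronger readings are tempting, and the documents do not support them.
- **A reader might infer that the design is faulty for want of an education-only arm.** The stated question is blood against urine, and two arms can answer it.
- **A reader might infer that every participant self-monitors.** Practices are allocated to a programme with a monitoring module, and participants may swap methods or stop. Those who stop select themselves, so they do not form a randomised reference group.
- **A reader might attach a power figure.** With SD 1.5%, design effect 1 + (5 − 1) × 0.05 = 1.2 and 170 per arm, SE = 1.5 × √(2 × 1.2/170) = 0.178. The chance of declaring equivalence at zero difference is then 2Φ(0.5/0.178 − 1.645) − 1, about 75%, with a 90% interval, or about 60% with a 95% interval (1.96 in place of 1.645). The article does not say which interval applies. Either figure only restates that the result depends on *b* − *u*, so it is no ground for the point.
- **A reader might infer that the recommendation extends to the standard programme.** That programme has a 20-minute monitoring session, against 100 minutes in the trial. The study intervention is defined as the programme with the specific monitoring sessions, and the natural reading of the implications section is that version.

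**Conclusion.** The point holds as one about claims and permitted conclusions, not about the design. The trial can estimate SMBG relative to urine testing. It cannot estimate what SMBG adds to structured education, and an equivalence result would not show that either method adds anything. The consequential place is the implications section, where equivalence becomes evidence for recommending SMBG. The headline sentence and the later phrase in the Discussion are lesser faults, partly corrected by the text around the first.

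The size is qualitative: nothing in the sample size, the margin or the analysis turns on it. The conclusion rests on the two-arm allocation as stated and on the article giving no direct figure for urine testing against no monitoring. It would remain with a narrower margin.

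**What to change.** - **Discussion, particular-strength sentence and the later phrase on benefit within an education programme:** state the contribution or benefit as that of SMBG relative to urine testing.
- **Implications of the hypothesis:** state that equivalence means only that the two methods do not differ in HbA1c by more than the margin; that it is not evidence that either method improves HbA1c over the education programme alone; and that equivalence by itself does not support recommending SMBG. If a view on whether monitoring works is to be offered, attribute it to the outside evidence and say that this evidence is mixed.

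No third arm, added analysis or change in sample size is needed. The cost is a few sentences and a narrower headline claim.
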